### Blinding

Due to the nature of the intervention, participants, implementers and research partners should be considered unblinded. The statistician performing the main trial analysis will be blind to allocation.

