### Study partners

Our collaboration currently involves five partners, convened by the International Rescue Committee (IRC), an international non-governmental organization (NGO) delivering services in conflict-affected settings. Since 2016, IRC has been developing and piloting the EmpaTeach intervention in conjunction with the Behavioural Insights Team (BIT), a team of UK and USA based behavioural scientists. IRC implements the EmpaTeach intervention in this study. Innovations for Poverty Action (IPA) is the quantitative data collection partner for the study and collaborates on a range of projects with IRC. IPA is an international organisation which facilitates data collection for large scale quantitative research projects via its local country offices. IRC has been working with IPA to collect data in relation to its projects in Africa for over 5 years.

In July 2018, the London School of Hygiene and Tropical Medicine (LSHTM) was invited to join the collaboration to conduct an independent evaluation of the EmpaTeach intervention. LSHTM leads the trial and quantitative aspects of the process and economic evaluations; the Tanzania National Institute for Medical Research leads the qualitative aspects of the research.

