### Survey procedures

We will conduct surveys at three time points: a baseline prior to the intervention, a midline soon after the 10-week intervention; and an endline at least 6 months after the end of the intervention (Fig. 1).

Data will be collected at each time point from students and teachers during individual interviews by Kiswahili or Kirundi-speaking interviewers. Before each round of data collection interviewers will receive 2 weeks of in-depth training on how to ask sensitive questions in a non-judgemental manner, survey procedures, and child protection procedures. Individual interviews will be done using a questionnaire programmed into tablet computers. Interviews with students will be conducted at schools, in places where interviewer-participant pairs are out of earshot but within sight of others, to protect confidentiality and ensure child safety. Female interviewers will interview both male and female participants; male interviewers will interview only male participants.

Survey data collected by tablet will be stored on a password protected database that is online-accessible only to senior study personnel, and backed-up daily in encrypted folders. The electronic master database will be held on IPA’s secure server. Devices will be password protected at all times to prevent accidental discovery of personal information by third parties during data collection. Data will contain identifying information as we intend to link data from individuals over time, and to link individual survey data with administrative data held by schools.

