#### Governance

LSHTM is the sponsor for the trial. The study has been approved by the London School of Hygiene and Tropical Medicine (16000–1) and Tanzania National Institute for Medical Research (NIMR/HQ/R.8a/Vol. IX/2920) ethics committees. The trial is overseen by KD and managed by CF. EA is the study statistician. IPA manages data collected during the study, including data related to child protection referrals. IPA staff report to LSHTM staff during the study to ensure independence. IRC initiated the study and are responsible for implementing the intervention and also for child protection responses as described above. The trial is overseen by a trial steering and data monitoring committee; comprised of an independent chair, a statistician, an expert member, the PI, the study manager and study statistician. Representatives from NIMR, IRC, IPA and BIT are invited as observers at the discretion of the chair.

The main data monitoring concerns for this trial relate to ensuring that cases where children have been exposed to severe forms of violence are detected and referred for additional support services. Detecting these children is likely to occur during data collection, rather than during the intervention implementation itself. Comprehensive referral plans have been developed for referral of cases detected during research as described above. At the end of the study, the number of referrals and a summary of actions taken will be presented to the trial steering committee and the LSHTM and NIMR ethics review boards. It is important to note that normally responses to child protection concerns would not be handled by the same NGO implementing the intervention. However, in Nyarugusu Refugee Camp, IRC is responsible for the provision of both education and violence response services.

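### The blanket statement that research partners are unblinded covers the data-collection organisation, so interviewers who elicit the self-reported primary outcome may know each school's arm

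*Protocol article*

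**What the plan says.** The Blinding section of the protocol article gives the kind of intervention as its reason and states that "participants, implementers and research partners should be considered unblinded". It names one exception: "The statistician performing the main trial analysis will be blind to allocation".

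The Study partners section shows who the research partners are. It says that "Innovations for Poverty Action (IPA) is the quantitative data collection partner for the study" and, of a different organisation, that "IRC implements the EmpaTeach intervention in this study". The Governance section adds that "IPA staff report to LSHTM staff during the study to ensure independence".

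On how the outcome is obtained, the Survey procedures section says: "Data will be collected at each time point from students and teachers during individual interviews by Kiswahili or Kirundi-speaking interviewers". It also says: "Interviews with students will be conducted at schools". The Outcomes section defines the primary outcome as past-week physical violence by students' self-report on a modified ICAST, assessed at midline. Emotional violence and depressive symptoms, both secondary outcomes, are also questionnaire measures answered by students.

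**The concern.** Whether a child discloses recent violence to an adult can depend on how the question is put, how far it is followed up and what the adult expects to hear. For this outcome the interviewer acts as the outcome assessor. If interviewers know that a school had EmpaTeach and expect less violence there, fewer recorded disclosures could look like an effect of the intervention. The same route is open for emotional violence and depressive symptoms.

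The one safeguard that the Blinding section states comes too late in the chain. A masked statistician cannot remove a difference that entered the data at interview, and a GEE model that allows for clustering by school does not remove it either.

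The stated reason also fits the groups unevenly. Teachers know whether they attended sessions, and the implementer must know where to deliver them. Interviewers have no such need. This is more than an article leaving detail to a fuller document, because the article states a rule and a reason, and the reason does not extend to everyone under the rule.

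**Working it through.** **Who is covered.** The sections fit together as follows.

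1. Blinding: research partners are treated as unblinded, and only the main-analysis statistician is masked.
2. Study partners: the data-collection organisation is a partner and is not the implementer.
3. Survey procedures and Outcomes: the primary outcome is collected by individual interview at school.
4. No section says that interviewers will be told the allocation, and none says that it will be kept from them.

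Steps 1 to 3 place the interviewers under the unblinded heading. Step 4 means that this is an inference from a general sentence, so the correct strength is that they may know the arm.

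**The plan's own figure.** Inputs from the Sample size section: 25 schools, 50 students per school, ICC 0.10, prevalence 50%, significance level 0.05, power 80%, detectable difference 19%. The article does not state sidedness, so I take the test as two-sided. The Abstract gives an allocation ratio of about 1:1, which is 12.5 schools per arm on average.

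- Design effect = 1 + (50 − 1) × 0.10 = 5.9.
- Effective students per arm = 12.5 × 50 / 5.9 = 105.9.
- Solving the two-proportion power formula for 80% gives a detectable difference of 18.8 points (19.2 with 12 schools per arm, 18.5 with 13).
- Power at 50% versus 31% is 80.9%.
- If 19% were relative (50% versus 40.5%), power would be only 28%. The figure is therefore in percentage points, and it reproduces.

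**Standard error of the difference.** From the stated figure: 19 / (1.96 + 0.842) = 6.78 points. Directly, with no true effect: √(2 × 0.25 / 105.9) = 0.0687, or 6.87 points. The two agree closely; the first is used below.

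**Illustration of differential elicitation.** Assume no true effect, 50% true prevalence in both arms, and recorded disclosures in intervention schools lowered by 5%, 10% or 15%. These three values are assumptions; the documents give none. With b = bias / 6.78, the two-sided rejection probability is 1 − Φ(1.96 − b) + Φ(−1.96 − b).

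| Relative reduction (assumed) | False difference | Share of 19 points | b | False-positive rate |
|---|---|---|---|---|
| 5% | 2.5 points | 13% | 0.37 | 6.6% |
| 10% | 5 points | 26% | 0.74 | 11% |
| 15% | 7.5 points | 39% | 1.11 | 20% |

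**The case against.** The strongest reply is that the Blinding sentence is a candid disclosure about organisations and not a decision to brief field staff on allocation. That is a fair reading. A reader might infer that interviewers will be told the arm, but the article does not say so.

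A second reply is that masking may not last. Schools are allocated at a public meeting of headteachers, students are interviewed at their schools, teachers are interviewed too, and one session calls for a classroom-rules poster on the wall. All of this stands. It limits what masking can achieve, but it does not explain why withholding the allocation should not be attempted.

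Third, there are safeguards. Interviewers have two weeks of training before each round, including how to ask sensitive questions without judgement. The questionnaire is programmed on tablets, and data-collection staff report to the sponsor and not to the implementer. These reduce the scope for differential probing, though none of them is masking.

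Fourth, participants are themselves unblinded and the outcome is self-report, so masking interviewers would leave respondent bias untouched. This also stands.

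A reader might further infer that interviewers, or the balance of male and female interviewers, could differ between arms. The article does not support that. It says only that "Female interviewers will interview both male and female participants; male interviewers will interview only male participants", which applies equally in both arms, and deployment is field detail that an article may leave out.

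**Conclusion.** The point holds as a bounded design improvement. As written, nobody who elicits the primary outcome is stated to be masked, and the reason given does not account for that in the case of interviewers who deliver nothing and work for a body separate from the implementer. Their knowledge of the arm is possible under the text, not established by it.

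The size of any interviewer bias is unknown. The range of about 6.6% to 20% rests on an assumed differential of 2.5 to 7.5 points, an assumed direction, no true effect and a two-sided test. It shows how sensitive a trial of this size would be. A reader might take it as an estimate of the trial's real error rate, and nothing in the article supports that. Nor would it be right to conclude that the student-reported results could not be interpreted at all: the training, the tablet questionnaire and the reporting line all count in the plan's favour. The 19-point detectable difference is correct, and neither the sample size nor the analysis model needs to change.

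**What to change.** - **Blinding section:** separate student-survey interviewers from the other research partners, and state that they are not told the allocation.
- **Survey procedures section:** if the student questionnaire asks about exposure to EmpaTeach, for instance to assess contamination, place those questions after the violence and mood modules on the tablet.
- **Recording:** have interviewers note any unmasking or their guess of the arm, and report the result as partial masking.

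The article gives no cost for this. My judgement is that it is small: a sentence in the existing training, a question order on the existing tablets and one extra recorded item, with no extra staff. The drawback is that masking will be incomplete for the reasons given above and must not be reported as full assessor blinding. Bias from unblinded respondents would still have to be acknowledged as a limitation.

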### Contamination

We have chosen to randomise at the school level to minimise possible contamination. As the intervention is mainly delivered to groups of teachers in a targeted way, we do not expect much natural diffusion due to the nature of the intervention itself. We expect that teacher transfer will be our main possible source of contamination. Based on 2017 data, 10% of teachers transferred to a different school during the school year (although we are informed that these levels are higher than normally expected due to a reorganisation of schools in 2017). We recognise that this contamination potentially reduces the observable effect, and we intend to collect data to assess whether contamination may have taken place.

### Statistical methods

All primary analyses will be carried out according to the principle of intention-to-treat (ITT) and using Generalised Estimating Equations (GEE) to take into account clustering at the school level. Our main analysis of the primary outcomes, and other secondary outcomes will be based on cross-sectional analyses comparing the outcome at midline for two main reasons. One, the intervention will be delivered to all teachers in a given school and is thus expected to impact on all pupils, not just on those pupils who were present at baseline. Two, the literature suggests that in cluster randomised trials, when migration into or out of the clusters is high over time, the baseline cohort may not remain representative of the cluster and therefore repeated cross-sectional analysis is preferred to minimise bias. However, where possible we will link student data across time points and will use analyses that include all students at all time-points, which essentially provides a repeat cross-sectional analysis with a nested longitudinal cohort.

Data will be analysed using multivariate regression models. We will carry out unadjusted analyses and analyses adjusted for any stratification factors and other pre-hypothesised potential confounders as covariates. Formal testing will be restricted to a pre-specified number of the secondary outcomes. A further small number of exploratory subgroup analyses will be specified in advance. These will include subgroups by sex, ethnicity, primary versus secondary school, baseline level of violence and student’s disability.

Other secondary analyses will include teacher outcomes and will be carried out according to the principle of ITT using a similar approach to modelling as described for the student outcomes.

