**Methods:**

We will conduct a two-arm cluster randomized controlled trial (RCT) with parallel assignment and an approximately 1:1 allocation ratio. All primary and secondary schools in Nyarugusu will be invited to participate. Whole schools will be stratified according to whether they are Congolese or Burundian, and primary or secondary schools, then randomised to active intervention or wait-list control conditions via a public meeting with headteachers. We will collect survey data from *n* = 500 teachers and at least *n* = 1500 students before the intervention, soon after, and at least 6 months after the end of the intervention. The primary outcome measure will be students’ self-reports of experience of physical violence from school staff in the past week, measured using a modified version of the International Society for the Prevention of Child Abuse and Neglect Screening Tool-Child Institutional at the first follow-up after the intervention. Secondary outcomes include emotional violence, depressive symptoms and educational test scores. Analysis will be intention to treat, using repeat cross-sectional data from individuals.

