### Sample size

Assuming 25 of 27 schools in the camp agree to participate; an intra-class correlation coefficient (ICC) of 0.10 [10]; a significance level of 0.05; 80% power; and a 50% prevalence of past week violence, [10] we would be able to detect a 19% difference in prevalence of physical violence from school staff to students if we surveyed 50 students per school. We thus plan to invite 60 students per school to participate to allow for non-response (n = at least 1500 in total). We also plan to survey about 20 teachers per school (*n* = 500 teachers in total) to explore the intermediate outcomes of the intervention. We planned to stratify randomisation by predictive factors to ensure that the ICC is at the lower end of the range, including whether school are mainly Congolese or Burundian, and whether they are primary or secondary.

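### GEE is fixed as the primary method for about 25 schools with no small-sample correction named; uncorrected, the strata-adjusted test would run at about 8 to 9.5% instead of 5%

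*Protocol article*

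**What the plan says.** Statistical methods in the protocol article states that all primary analyses follow intention to treat, "using Generalised Estimating Equations (GEE) to take into account clustering at the school level". It plans both unadjusted analyses and analyses adjusted for the stratification factors and other pre-hypothesised confounders, and does not say which is the primary test. Teacher outcomes are to be modelled in a similar way.

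The Sample size section sets the scale. For the number of clusters it writes "Assuming 25 of 27 schools in the camp agree to participate"; for the clustering it takes "an intra-class correlation coefficient (ICC) of 0.10"; for the test it takes "a significance level of 0.05"; and for the outcome it takes "a 50% prevalence of past week violence". On a sample described as "if we surveyed 50 students per school", its conclusion is that "we would be able to detect a 19% difference in prevalence of physical violence from school staff to students". The Abstract gives "an approximately 1:1 allocation ratio", so about 12 against 13 schools. Randomisation is stratified by two school-level factors, Congolese or Burundian and primary or secondary. The Sample size section describes the stratifying factors as predictive.

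The article names no variance estimator, working correlation, reference distribution or degrees of freedom for the GEE.

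**The concern.** The usual GEE test divides the estimate by a sandwich standard error and refers the ratio to the normal distribution. That is justified as the number of clusters grows. With about 25 schools the sandwich variance is biased downwards, and the normal reference ignores the uncertainty in that variance. Each school-level covariate makes both problems worse, and both stratification factors are school-level.

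If nothing corrects for this, p-values are too small and confidence intervals too narrow in the adjusted analyses of the primary and secondary outcomes. The result matters: the article makes delivery to the control schools depend on the intervention proving effective (and on funding), and it foresees scale-up through the implementing organisation's work in 40 countries.

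**Working it through.** **Inputs from the article.** 25 schools (27 at most), 50 students per school, ICC 0.10, prevalence 50%, level 0.05, power 80%, about 1:1 allocation, two binary stratification factors.

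**Assumed, because not stated.** Two-sided test; schools per stratum 8/5/9/3, with 10/4/9/2 and 7/6/6/6 as alternatives; beta-binomial variation between schools.

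**Step 1: reproduce the stated 19%.**
- Design effect = 1 + (50 − 1) × 0.10 = 5.9.
- Effective sample per arm = 12 × 50 / 5.9 = 101.7 and 13 × 50 / 5.9 = 110.2.
- Two-proportion normal approximation (pooled variance under the null) at 80% power: detectable difference 18.8 points with 12/13 schools and 19.2 points with 12/12.
- Power at 19 points: 80.9% and 79.3%.

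The stated figure reproduces as 19 percentage points with large-sample quantiles.

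**Step 2: false-positive rate of the uncorrected test.** School prevalences were drawn from Beta(4.5, 4.5), which has mean 0.5 and ICC 1/(1 + 4.5 + 4.5) = 0.10, with no intervention effect. A logistic GEE was fitted and the sandwich Wald z test applied at 0.05. There were 20,000 runs per scenario, so the Monte Carlo standard error near 9% is √(0.09 × 0.91 / 20,000) = 0.2 points.

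| Scenario, uncorrected z test | Unadjusted | Two main effects | Four strata |
|---|---|---|---|
| 25 schools, three sets of stratum sizes | 6.8–7.4% | 8.3–8.6% | 9.1–9.6% |
| 25 schools, unequal school sizes (CV 0.3) | 6.8% | 8.6% | 9.3% |
| 27 schools | 7.0% | 8.2% | 8.7% |
| 25 schools, strata differ in prevalence (60/40/55/30%, ICC 0.07 within strata, stratified allocation) | 3.2% | 8.2% | 9.5% |

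A cross-check with a standard GEE routine on individual data (exchangeable correlation, 25 schools, 6,893 runs) gave 7.4%, 8.6% and 9.5%. A separate simulation gave about 6.5% unadjusted and 8 to 9.5% adjusted.

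**Step 3: what a correction does (25 schools).**
- t reference alone on the uncorrected variance: 5.4–6.0% unadjusted and 6.6–7.7% adjusted. This is not enough for the adjusted model.
- Kauermann-Carroll variance with t on schools minus parameters: 4.6–5.1%, adjusted or not, when the strata do not differ in prevalence.
- The same correction when the strata do differ: 4.7% with two main effects and 5.1% with four strata. The unadjusted test falls to 2.0%.

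**Step 4: effect on the detectable difference.** Replace the normal quantiles (1.960 + 0.842 = 2.802) by t quantiles on 25 − 2 = 23 df (2.069 + 0.858 = 2.927), using the unpooled variance. With 12/13 schools the detectable difference is 19.4 points. The normal approximation gives 18.8 points with pooled variance, or 18.6 with the same unpooled variance.

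**The case against.** The strongest objection is that the article is silent and does not reject a correction. A condensed protocol article commonly leaves the variance estimator and degrees of freedom to the analysis plan, which is not shown. A GEE with a corrected variance and a t reference is still a GEE, so the quoted sentence is compatible with a valid test. This stands. A reader might infer that the sponsor will use no correction and that the trial's real significance level is therefore 9 to 10%. The document supports neither inference.

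Three further limits also stand:
- Rates above 9% need 25 schools and four stratum indicators. Two main effects give 8.2 to 8.6%, and with all 27 schools no adjusted rate exceeds 8.7%.
- The unadjusted figure of about 7% assumes strata that do not predict the outcome. The article itself calls the stratifying factors predictive. In the example where they are, the unadjusted test rejects in only 3.2%.
- The other confounders are not said to be school-level, so they cannot be counted as making the problem worse.

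What remains is that the article fixes a method whose ordinary form does not hold the stated level at the number of schools it plans for. If the strata are predictive, the two planned analyses err in opposite directions, and the article does not say which one decides.

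**Conclusion.** The point holds conditionally. Unless a small-sample correction is applied, the strata-adjusted GEE would reject a true null hypothesis in about 8 to 9.5% of trials against a nominal 5%. The unadjusted GEE would reject in about 6.5 to 7.5% if the strata carry no information on the outcome, and below 5% in the example where they do. The figures rest on a two-sided test, the assumed stratum sizes and beta-binomial clustering at the planned ICC of 0.10. Changing the stratum sizes, making school sizes unequal or using 27 schools moved them little.

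The sample size needs no rework. A reader might infer that the 19% figure is wrong, but it reproduces, and a t reference shifts it by about half a point.

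This is a low-cost improvement to a stated method. It does not show that the sponsor's eventual analysis is invalid.

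**What to change.** In Statistical methods, state that:
- the primary test is the GEE adjusted for the stratification factors, with their coding given (two main effects or four strata);
- the variance is corrected for small samples, for example by Kauermann-Carroll;
- the reference is a t distribution on the number of schools minus the number of school-level parameters (with 25 schools, 25 − 4 = 21 df for two main effects or 25 − 5 = 20 df for four strata, counting intercept and arm);
- confidence intervals are computed on the same basis.

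If the analysis plan already specifies this, a sentence confirming it is enough.

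The cost is a few lines of text and slightly wider intervals. The detectable difference in the Sample size section can be restated as about 19.4 points (t on 23 df, 12/13 schools), which is at most a minor change.

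### The primary midline model does not name each school's baseline prevalence of violence as a covariate, although the stated reasons for a midline analysis do not rule it out

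*Protocol article*

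**What the plan says.** All references are to the Protocol article.

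- **Survey procedures** sets three survey rounds: "a baseline prior to the intervention, a midline soon after the 10-week intervention", and an endline at least six months after the intervention ends. **Outcomes** places the primary outcome, student-reported past-week physical violence, at midline.
- **Statistical methods** uses GEE to allow for clustering by school and says that the main analysis "will be based on cross-sectional analyses comparing the outcome at midline for two main reasons". The reasons are that the effect is expected in all pupils, including those who were not there at baseline, and that with high migration a baseline cohort may stop representing its school.
- The next sentence adds that students will be linked where possible and that analyses will take in every student at every round. It does not say how these relate to the main analysis.
- Unadjusted and adjusted analyses are both planned. The adjusted ones use the stratification factors and further potential confounders that are not named. Baseline violence is named only among the exploratory subgroups: "primary versus secondary school, baseline level of violence".
- **Sample size** takes no credit for baseline adjustment. It does stratify by factors expected to predict the outcome, in order to keep the ICC low.

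**The concern.** About 25 schools are randomised. At the planned ICC and sample per school, most of the variance of a school's observed prevalence comes from true differences between schools. With so few units, the arms can differ by chance in how violent their schools were at the start. The school's own pre-intervention level of the outcome is the most direct predictor of its midline level, and it will already have been measured.

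The two reasons given for a midline cross-section concern which students to analyse. A school-level covariate leaves that choice alone: the analysis population is still every student surveyed at midline, and each of them belongs to a school with a baseline figure. At stake are power and the width of the confidence interval.

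The all-rounds sentence adds an ambiguity. A reader cannot tell whether it supplements the midline comparison or modifies it, so more than one model could later be presented as the main one.

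**Working it through.** **Inputs from Sample size.**

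- Number of clusters: "Assuming 25 of 27 schools in the camp agree to participate".
- Clustering: "an intra-class correlation coefficient (ICC) of 0.10".
- Error rates: "a significance level of 0.05; 80% power". I take the test as two-sided.
- Control-arm level: "a 50% prevalence of past week violence".
- Stated detectable difference: 19%, with 50 students surveyed in each school.

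I take the split as 12 and 13 schools.

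**Input not in the document.** CAC is the correlation between baseline and midline of the true school prevalences. It is an assumption, shown over a range.

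**Step 1: reproduce the stated figure.** Design effect = 1 + (50 − 1) × 0.10 = 5.9. Detecting 50% v 31% needs 104 per arm under individual randomisation; 104 × 5.9 = 613.6 per arm, or 2 × 613.6 / 50 = 24.5 schools. Solving for the difference with 12 and 13 schools gives 18.8 points, with 81% power at 19 points. The stated 19% therefore reproduces as absolute percentage points. With t critical values on 23 df it is 19.4 points.

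**Step 2: how well an observed baseline prevalence reflects the true one.** Between-school share of the variance of a school's observed prevalence = 0.10 / (0.10 + 0.90/50) = 0.10 / 0.118 = 0.847, which is 5/5.9.

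**Step 3: effect of the covariate, taking different students in each round.** Correlation of observed school prevalences r = 0.847 × CAC; variance factor = 1 − r². For example, at CAC 0.5, r = 0.424 and 1 − 0.424² = 0.82. The detectable difference is then solved again.

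| CAC | r | Variance factor | Detectable difference (points) | Power at 19 points | Detectable difference, t test, one df spent (points) |
|---|---|---|---|---|---|
| 0 | 0 | 1.00 | 18.8 | 81% | 19.4 |
| 0.3 | 0.25 | 0.94 | 18.2 | 83% | 18.8 |
| 0.5 | 0.42 | 0.82 | 17.1 | 88% | 17.7 |
| 0.7 | 0.59 | 0.65 | 15.3 | 94% | 15.8 |
| 0.8 | 0.68 | 0.54 | 14.0 | 97% | 14.5 |

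**Step 4: allow for the strata.** If stable stratum differences already explain part of the between-school variance, the stratum terms capture that part. Suppose they explain 30% (assumed). The remaining between-school component is 0.07, so the share in Step 2 becomes 0.07 / (0.07 + 0.018) = 0.795.

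- Total CAC 0.5: residual CAC = (0.5 − 0.3) / 0.7 = 0.29; r = 0.23; variance factor 0.95.
- Total CAC 0.8: residual CAC = (0.8 − 0.3) / 0.7 = 0.71; r = 0.57; variance factor 0.68.
- If strata explained 50% and total CAC were 0.5, residual CAC would be 0 and there would be no gain.

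The table in Step 3 applies as it stands only if ICC 0.10 and CAC are read as within-stratum values.

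**Step 5: cost of the covariate.** Simulated school-level analyses (25 schools, assumed strata of 9, 3, 9 and 4 schools, no stratum effect, t test, true difference 19 points, 4,000 trials per scenario) gave 76–78% power with strata only. Adding baseline prevalence gave 82% at CAC 0.5, 90% at 0.7 and 95% at 0.8. At CAC 0.3 there was no net change, and at CAC 0 power fell by about 3 points. Gain and cost thus cancel at a CAC of about 0.3, which is also close to the residual CAC of 0.29 in the first case of Step 4.

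**The case against.** The strongest case against is that the article leaves its covariate list open. School baseline prevalence would fit among the unnamed covariates, nothing excludes it, and a journal article commonly leaves such a list to an analysis plan that is not shown. That stands, and an unnamed covariate would be no finding by itself. What remains is that the article does fix the main analysis as a midline comparison, argues for it on grounds that do not touch a school-level covariate, and does not place the all-rounds analyses relative to it.

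A reader might infer that the baseline survey is never used. The text does not support that: it promises analyses including all students at all rounds and a subgroup by baseline violence.

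A reader might also infer that the midline comparison is biased. It is not. Randomisation makes it valid on average; the covariate reduces the influence of chance imbalance.

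Nor is the gain free or assured. It rests on a correlation the document does not give. Strengths and limitations reports school reorganisations with large transfers of students in 2017 and 2018, and more of these could lower it. The stratifiers were chosen because they predict the outcome, so some of the gain may already be taken. Finally, the sample size calculation reproduces without any baseline credit, so no stated figure is wrong. All of this limits the size of the point. It does not remove the case for naming the covariate, because the downside is small and the upside can be large.

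**Conclusion.** The point holds as a recommendation on efficiency and clarity. The main analysis is a midline comparison whose primary model does not name school baseline prevalence, the two stated reasons do not exclude it, and the status of the all-rounds analyses is unclear.

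Under the plan's own ICC and sample per school, the covariate would cut variance by about 18% at CAC 0.5 and 46% at CAC 0.8. The cut is about 6% at 0.3 and nil at 0. If the strata explain 30% of the between-school variance, the cuts at total CAC 0.5 and 0.8 become about 5% and 32%; the first would be roughly offset by the lost degree of freedom. The short interval between baseline and midline makes a useful correlation plausible, but the document gives no figure for it.

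**What to change.** Before midline data are seen, state in the protocol or analysis plan that:

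1. The primary model is the GEE on all students surveyed at midline, adjusted for the stratification factors and the school's baseline prevalence of past-week physical violence. For each secondary survey outcome, use the school's baseline mean of that outcome.
2. The analysis of all students at all rounds is secondary.
3. The baseline-violence subgroup is defined by the same school-level variable. Every midline student then has a value, whether or not the student can be linked to a baseline interview.

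A short rule for a school that is split, merged or newly opened between rounds would keep the covariate defined.

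The cost is wording and one of about 23 school-level degrees of freedom, with a small loss of power if CAC is near zero. No further data are needed.
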